# Effects of exercise on symptoms of anxiety, cognitive ability and sick leave in patients with anxiety disorders in primary care: study protocol for PHYSBI, a randomized controlled trial

**DOI:** 10.1186/s12888-019-2169-5

**Published:** 2019-06-10

**Keywords:** (n=3-10), Anxiety, Exercise, Cognitive function, Dose-response, Intervention

## Abstract

**Background:**

Anxiety disorders are common and associated with reduced quality of life, impaired physical and mental health and an increased economic burden for society. While evidence exists for the effectiveness of exercise treatment for depression, there is a need for high-quality randomized clinical trials (RCT) with a focus on anxiety disorders. Further research is also warranted regarding outcomes of cognitive function, other health-related variables, dose-response effects, work ability and potential mechanisms.

**Method/design:**

Using a parallel, RCT design with three assessment points (baseline, post-intervention and one-year follow-up), we aim to assess the effect of a 12-week exercise intervention in primary care patients with anxiety disorders (*n* = 180), diagnosed using the Mini International Neuropsychiatric Interview (M.I.N.I; Swedish version 6.0.0d DSM-IV). Participants are randomly assigned to three physical exercise groups: one low-intensity training group, one moderate- to high intensity training group and one control non-exercise group. Assessments include measures of anxiety symptoms, cognitive function, physical health variables such as cardiovascular fitness, sick-leave and levels of hormones/cytokines in blood samples.

**Discussion:**

Findings from this study will provide novel insights regarding the effects of exercise treatment on not only anxiety symptoms but also other outcomes including mental and physical health, cognitive function, dose-response effects, work ability/sick leave and on biomarkers that may help explain underlying mechanisms.

**Trial registration:**

The trial was registered at ClinicalTrial.gov NCT03247270 August 8, 2017.

**Electronic supplementary material:**

The online version of this article (10.1186/s12888-019-2169-5) contains supplementary material, which is available to authorized users.

## Background

Anxiety disorders are the most common mental disorders [1], with global prevalence figures ranging from 4 to 25% [2]. Data from the US indicate that one out of three will be affected by an anxiety disorder at some point during lifetime [1]. In a national survey of the Swedish adult population, 36% reported having anxiety issues [3] and lifetime prevalence for anxiety disorders in Sweden is estimated to be 25% [4]. In Sweden, it has been estimated that 70% of individuals who seek help for symptoms of anxiety and depression initially present in primary care [5] and costs for mental illness within primary care are on the rise [6].

Anxiety disorders substantially reduce quality of life and daily functioning [7] and are, among mental disorders, the second leading cause of years lived with disability [8]. They are also associated with elevated risks of cardiovascular disease [9] and premature mortality [10]. We have previously shown that anxiety disorders are associated with increased risk of future marginalization [11] as well as elevated mortality [12], emphasizing the importance of finding effective treatment strategies. Individuals with anxiety disorders frequently suffer from attentional problems, such as being easily distracted and unable to focus on ongoing tasks [13]. Moreover, impairments in cognitive function, including executive function and working memory, are often observed, which can be both a consequence and a symptom of anxiety [14–16]. Taken together, anxiety disorders place a considerable emotional, social, health-related and financial burden on both the individual and society.

The standard treatments for anxiety disorders include cognitive-behavioural therapy and pharmacological treatment [17]. Although these approaches often are effective in reducing anxiety symptoms, they may also be associated with treatment barriers and drawbacks. For example, nearly one third of patients do not respond to pharmacological treatment which may be associated with adverse side effects and noncompliance [17]. Patients may not wish to follow cognitive-behavioural therapy due to a reduced willingness to commit to treatment and stigmatization issues [18]. Collectively, these findings call for alternate complementary or stand-alone approaches to the treatment of anxiety disorders. Moreover, given the known association between anxiety disorders and cardiovascular disease, it is also essential to develop interventions that may target not only mental but also physical health problems in people with anxiety disorders. Exercise may represent an alternative, affordable and accessible treatment option for individuals with anxiety, both by itself and together with standard treatments. For clarification, *exercise* is a subset of physical activity that is planned, structured, repetitive and has a purpose of improving or maintaining physical fitness and *physical activity* is defined as any bodily movement produced by skeletal muscles that result in energy expenditure [19]. *Physical fitness* on the other hand is a set of attributes that are either health- or skill-related, including cardiovascular fitness and muscle strength.

Observational studies report an inverse association between physical activity and anxiety symptoms [20] and there is strong evidence for exercise in the treatment of depression [21]. Despite these findings, relatively little research has been focused on exercise in the treatment of anxiety. Nonetheless, meta-analyses of randomized controlled trials (RCTs) studying anxiolytic effects of exercise interventions in individuals with and without an anxiety diagnosis suggest that exercise is an effective treatment on its own, as well as combined with other therapies [22–26]. However, most of the interventions studies included in these meta-analyses are at high risk of bias. High-quality RCTs are needed to gain further understanding of the effects of exercise in treatment of anxiety [24] and to develop optimal exercise protocols.

Key gaps in the literature remain regarding the effects of exercise on other mental and physical health variables in patients with anxiety disorders including cognitive function, cardiovascular fitness, optimal exercise protocols, work ability/sick leave as well as the underlying mechanisms of the effect of exercise on anxiety symptoms. These are all issues that the current study aims to address. Given that cognitive function can be improved by exercise [27], the current study includes tests of executive function, creativity, response inhibition and cognitive flexibility. We will also evaluate the intervention effects on cardiovascular fitness, muscle strength, BMI and blood pressure. Further understanding of dose-response relationships is important for establishing optimal protocols for exercise treatments in patients with anxiety, instead of only having to rely on general public health guidelines. Since dose-response effects of exercise have been minimally researched and studies of dose-response are often inconclusive [22, 23], we include two intervention groups with separate intensity levels of exercise training. It is also highly relevant to evaluate the effects of exercise on work ability in patients with anxiety disorders, since reducing medical and sick-leave costs for anxiety disorders would liberate health care resources to be used elsewhere in an economically strained health care system. In order to gain further understanding regarding mechanistic aspects, treatment effect and prognosis, we will also investigate protein levels of trophic factors in blood samples, through which exercise may reduce anxiety. A broad spectrum of possible mechanisms exists, explaining the effect of exercise on anxiety including neurotransmitter, neuromodulator and psychological mechanisms [28], but the precise mechanism remains unclear.

We here propose an RCT study with varying intensity of exercise training in patients with anxiety disorders. To the best of our knowledge, this multifaceted study is the first study of its kind and it has the potential to provide novel and important contributions to existing scientific knowledge regarding how exercise may influence symptoms of anxiety, cognitive function, general health and work ability in patients with anxiety disorders.

### Research aims and hypothesis

The primary aim is to investigate the effects of an exercise intervention on anxiety symptoms, cognitive function, physical health and quality of life and work ability in primary care patients who fulfil criteria for anxiety disorders. A secondary aim is to analyse any potential correlation of factors in blood samples (hormones/cytokines) with anxiety symptoms and function data and to study possible dose-response effects in patients assigned to exercise of different intensities. Another secondary aim is to study mediating or moderating effects of cardiovascular fitness or other comorbidities and to analyse possible differential effects in sub-groups of participants (different initial cardiovascular fitness levels, ages and gender). In addition, health-economic analyses will be performed concerning health-related quality of life effects associated with the intervention.

Our main hypothesis is that an exercise intervention will reduce symptoms of anxiety and the number of days on sick leave, improve cognitive function and physical health variables. An additional hypothesis is that the effect will be larger for high-intensity exercise than for low-intensity.

## Methods/design

### Study design

This is a randomized, parallel, controlled superiority clinical intervention study with three assessment points (baseline, post-intervention and one-year follow-up). The study is ongoing and was registered under ClinicalTrial.gov NCT03247270 on August 8, 2017 (https://clinicaltrials.gov/ct2/show/NCT03247270). The protocol was prepared in accordance with the SPIRIT 2013 statement. [29] Participants are randomly assigned to an exercise program of one low-intensity training group, one moderate- to high intensity training group and one control non-exercise group, with 1:1:1 allocation. Assessments and interventions are conducted at Primary Care Rehab (Närhälsan Primary Care) in Gothenburg, Sweden. Figure 1 shows the study design of the trial.

**Fig. 1 Fig1:**
[figure not shown]
Flow chart of study design

### Participants

Individuals who seek help for anxiety issues at six primary care centres in southwest Sweden (Region Västra Götaland and Region Halland) are recruited. The patients are informed by their general practitioner (GP) or psychologist about the possibility of study participation and those expressing interest are provided with the study physician’s phone number. Recruitment started in May 2017 and will continue until March 2020. Potential participants are then contacted by the study psychiatrist or nurse, who have no healthcare provider relationship to the patient.

Diagnoses and comorbidities are then determined by the study psychiatrist using the Mini International Neuropsychiatric Interview (M.I.N.I; Swedish version 6.0.0d DSM-IV), a short structured diagnostic interview with high reliability and validity [30]. Patients aged 18–65 diagnosed with anxiety disorders, including panic syndrome (F41.0), generalized anxiety (F41.1), mixed anxiety- and depression (F41.2 and F41.3), as well as anxiety NOS (F41.9) are included in the study.

Exclusion criteria include physical difficulties that preclude participation in the present exercise program, pathological electrocardiogram (ECG) including significant Q waves, ST-T changes, atrial fibrillation and left bundle-branch block, use of beta blockers, pregnancy, as well as previous psychiatric illness including bipolar disorder and psychotic disorders, ongoing substance abuse, ongoing burnout syndrome, and increased risk of suicide as assessed by the GP. An additional exclusion criterion is baseline physical activity level exceeding one exercise occasion per week. Individuals with and without ongoing treatment with psychoactive medication are included. Supportive contact, for example with a health center nurse, is not an exclusion criterion but individuals with ongoing psychotherapy are not included unless, after consultation with their GP, they can take a break in therapy for the duration of the 12-week intervention. Participant retention and adherence is promoted by exercise encouragement from the study physiotherapists, the possibility to receive personal results after study completion and reminders for follow-up assessment via letter, telephone and text message. The reasons for all eventual non-adherence and non-retentions will be documented.

### Intervention

Using computer generated randomisation (http://www.randomizer.org), patients are randomized into three groups: 1) Intervention I: 12-week exercise program with low-intensity training 3 times per week for 45 min; 2) Intervention II: 12-week exercise program with moderate to high-intensity training 3 times per week for 45 min; 3) Control group: a single physiotherapy session with general advice about physical activity. Participants are then informed by phone if they belong to an intervention group or the control group. Both intervention groups include cardiorespiratory and resistance training, and participants in group II are also encouraged to perform an additional running session per week. Participants in the control group are encouraged to start exercising after the study is completed and also receive a 3-months membership at a training facility, but are discouraged of actuating other exercise programs during the trial. All three groups self-report physical activity during the study. For participants in the intervention groups, the study physiotherapists designed individualized exercise programs during a one-to-one session with the patients on one occasion. The exercise program is designed as a circuit training with 12 stations, repeated twice (45 s workout, 15 s for transportation between stations and 1 min rest between the two laps). It also includes 10 min of warm-up exercises and 5–10 min of cool down and stretching exercises. Cardiorespiratory exercises include step-ups, lunges, jump rope, burpees, step touches side-to-side and step-touches on step board. Resistance training exercises include squats, abdominal plank position, hip lifts, crunches, row exercises and push-ups. Participants in intervention group I and II exercise separately in group sessions in the gym with the physiotherapist according to a predetermined schedule. A pulse-watch and the Borg RPE scale are used to monitor level of exertion to ensure appropriate exercise intensity. For intervention group I, the intensity level corresponds to 1.5–2.9 metabolic equivalents (METs), a Borg rated perceived exertion (RPE) of 10–14 and a maximal heart rate of 40–59%. The corresponding figures for intervention group II are 3.0–8.9 METs, Borg RPE 12–17 and 60–94% of maximal heart rate. Patients who are unable to participate in a session perform replacement exercises on their own.

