### Statistical analysis

Data will be presented using descriptive statistics, including the number of observations, means and standard deviations for continuous variables. For categorical variables, frequencies and percentages will be presented and data analysed using Chi-squared tests. Based on plotted histograms (confirming that the data may be considered as approximately normally distributed), continuous data will be analysed using a univariate general linear model (ANCOVA). In this model, treatment will be used as a categorical independent variable and baseline levels as covariates. Data will be presented as changes of means with corresponding 95% confidence intervals, standard deviations and *p*-values from group comparisons. The categorical outcome “treatment responsive” will be analysed using Chi-squared tests. A p-value below 0.05 will be considered statistically significant for all analyses. All statistical analyses will be performed by a statistician using SAS version 9.4 (SAS Institute, Cary, NC).

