In order to reduce the risk for worsening mental health or symptoms during the study we have a) assessed eligibility for study participation by a physician; b) excluded patients with heightened suicide risk; c) requested participants to contact research personnel if they feel worse; d) as intervention personnel, only included persons with knowledge regarding symptoms of worsening of anxiety and/or depression. If a patient experience worsening of symptoms, the subject will be excluded from the study and put in contact with the treating physician or psychologist. The study physician and physiotherapists will continuously inquire about and record any signs of worsening of mental health symptoms or side-effects.

Another experience from our previous intervention study on depression was the disappointment of being randomized to the control group. Therefore, the patients in the control group will have a single session with a physiotherapist and general advice about physical activity according to public health recommendations as well as a 3-month membership at a training facility for after study completion. Such a control condition, was chosen to potentially feel meaningful and inspiring to the participants. [47] A passive control group such as a wait-list design or treatment as usual are associated with negative influences on study results for nonpharmacological treatments, including a possible overestimation of the intervention effects and limited blinding possibilities. [48] Instead of an active control with an alternative behaviour, the current study has two separate interventions groups with different exercise intensities, a design that allows for comparison effectiveness depending on exercise dose as well as permits blinding for participants. All study participants will be informed about the results from the study, as will all participating professionals and the general medical community. Results will be published in peer-reviewed medical journals and results will be disseminated regardless of the magnitude or direction of effect. When writing manuscripts, ICMJE (International Committee of Medical Journal Editors) guidelines regarding authorship will be followed.

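### Only the high-intensity arm is encouraged to add a weekly run, so group II versus group I compares two exercise programmes and does not isolate intensity, as the additional hypothesis and dose-response aim are worded

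*Protocol article*

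**What the plan says.** The Intervention section gives both exercise arms the same frame: 12 weeks, three 45-minute sessions a week, and a 12-station circuit done twice. They differ in target intensity: 1.5–2.9 METs in group I and 3.0–8.9 METs in group II, with matching Borg and heart-rate bands. One further component goes to one arm only: "participants in group II are also encouraged to perform an additional running session per week". Its length, intensity and supervision are not given.

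Elsewhere the two arms are described by intensity:

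- Background, on why there are two exercise arms: "we include two intervention groups with separate intensity levels of exercise training".
- Research aims and hypothesis, secondary aim: "to study possible dose-response effects in patients assigned to exercise of different intensities".
- Research aims and hypothesis, additional hypothesis: "the effect will be larger for high-intensity exercise than for low-intensity".
- Ethical considerations, on the choice of control: "two separate interventions groups with different exercise intensities, a design that allows for comparison effectiveness depending on exercise dose".

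In the Statistical analysis section the outcome model is an ANCOVA in which "treatment will be used as a categorical independent variable and baseline levels as covariates".

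**The concern.** By assignment, group II differs from group I in intensity and also in encouraged frequency, volume and mode of exercise. The hypothesis and the aim name only the first of these. If group II does better, the randomised contrast supports the statement that the larger programme did better. It cannot say whether the higher intensity, the extra run or both were responsible, and no randomised comparison among these three arms can separate them.

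This bears on use of the result. The Background says that knowledge of dose-response is wanted to set optimal exercise protocols for these patients. A primary care service would want to know whether to raise the intensity of sessions or add another one. The run is also aerobic training, so it may act on cardiovascular fitness, which the trial treats both as an outcome and as a possible mediator or moderator.

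**Working it through.** The plan states no figure for this contrast, so there is none to reproduce. The check sets the two prescriptions side by side and then asks how large the extra component could be.

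**Sessions (from Intervention).** Scheduled: 3 × 12 = 36 in each arm. Encouraged runs in group II: 1 × 12 = 12 at full uptake.

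- Full uptake: 36 + 12 = 48, or +33%.
- Half uptake: 36 + 6 = 42, or +17%.
- Quarter uptake: 36 + 3 = 39, or +8%.

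These are prescribed counts. Actual counts may differ in either arm: the Participants section allows entry with up to one exercise occasion a week ("An additional exclusion criterion is baseline physical activity level exceeding one exercise occasion per week"), and only controls are discouraged from taking up other programmes.

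**Share of the MET-minute difference (illustration only).** Share = run MET-minutes ÷ (session gap + run MET-minutes), where session gap = weekly session minutes × (METs in II − METs in I).

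Assumptions not in the article: a run of 20 to 45 minutes, full uptake, a run at group II's MET value, and both arms at the same position in their bands. Midpoints are (1.5 + 2.9)/2 = 2.2 and (3.0 + 8.9)/2 = 5.95.

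Two bases are possible for the session minutes:

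- All 45 minutes differ by arm: 3 × 45 = 135 min a week.
- Only the circuit differs, with warm-up and cool-down alike: 2 × 12 × 1 min + 1 min rest = 25 min, so 3 × 25 = 75 min a week.

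| METs (I, II) | Gap, 135 min | Share, 20 to 45 min run | Gap, 75 min | Share, 20 to 45 min run |
|---|---|---|---|---|
| Bottom (1.5, 3.0) | 202.5 | 60/262.5 = 22.9% to 135/337.5 = 40.0% | 112.5 | 60/172.5 = 34.8% to 135/247.5 = 54.5% |
| Middle (2.2, 5.95) | 506.25 | 119/625.25 = 19.0% to 267.75/774 = 34.6% | 281.25 | 119/400.25 = 29.7% to 267.75/549 = 48.8% |
| Top (2.9, 8.9) | 810 | 178/988 = 18.0% to 400.5/1210.5 = 33.1% | 450 | 178/628 = 28.3% to 400.5/850.5 = 47.1% |

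At half uptake, with midpoints and the 135-minute base, the share falls to 59.5/565.75 = 10.5% to 133.9/640.1 = 20.9%. With no uptake it is zero.

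The table does not give bounds. If the two arms sat at different points of their bands, the range would widen. For example, with group I at 2.9 and group II at 3.0 METs, the 135-minute gap is only 135 × 0.1 = 13.5, and a 20-minute run gives 60/73.5 = 82%. With group I at 1.5 and group II at 8.9, the gap is 135 × 7.4 = 999, and the same run gives 178/1177 = 15%.

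**Analysis.** The ANCOVA has treatment and baseline only. It correctly estimates the difference between whole programmes. It is not at fault, but it cannot turn that difference into an effect of intensity.

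**The case against.** The case for leaving the text alone has four parts.

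- **The run is disclosed and only encouraged.** The article states it openly, and uptake could be near zero. That limits the likely size. It does not remove the mismatch, because the encouragement itself is assigned to one arm.
- **Dose can include volume.** The article speaks of dose-response and, under Ethical considerations, of exercise dose; it nowhere says that the arms are matched on volume or that intensity is isolated. This is fair, and the fault is loose wording more than a false statement. But the Ethical considerations sentence describes the arms by intensity, as do the aim and the hypothesis, and none of them mentions the run.
- **Higher METs for the same session time already mean more total work.** True: even without the run, group II does more. The run adds frequency, minutes and mode on top of that.
- **The consequence is small.** It touches one additional hypothesis and one secondary aim. This stands, and it sets the weight of the point.

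A reader might go further and infer that the comparison of the exercise arms is biased or invalid. The documents do not support that: the arms are randomised, and the contrast is sound for the programmes as prescribed. A reader might also infer that the run is known to drive the contrast, or, conversely, that session intensity always accounts for most of it. Neither follows, because run length, run METs and uptake are not stated and the shares in the table fall on both sides of one half.

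**Conclusion.** The point holds as a mismatch between the prescribed contrast and the wording of the claim. Group II versus group I estimates the effect of higher intensity plus an encouraged weekly run, relative to low intensity. It is valid as a programme comparison and does not isolate intensity.

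The firm figure is the session count: 36 scheduled in each arm, and up to 48 in group II if every encouraged run is done. The MET-minute shares (about 18–40% on the 135-minute base, up to about 55% on the 75-minute base, at full uptake) show only that the run need not be trivial. They rest on an assumed run length, full uptake, a run at group II's MET value and a common band position.

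Each exercise arm versus control, the main hypothesis and the sample size do not depend on this point.

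**What to change.** Restate the additional hypothesis, the dose-response aim and the reported group II versus group I contrast as a comparison of a higher-dose with a lower-dose exercise programme, and define the higher dose as higher intensity plus an encouraged weekly run. State that a difference between these arms will not be attributed to intensity alone.

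No change to the intervention, the randomisation or the ANCOVA is needed. If run uptake is described from the activity self-reports, that is a reporting detail. It should stay descriptive, because uptake arises after randomisation and adjusting for it would not recover an effect of intensity.

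The cost is a change of wording and a narrower dose-response claim.
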